### Protocol

The aim of this study is to evaluate and compare the effectiveness of kaleidoscope and virtual reality goggles to reduce dental anxiety in young children undergoing administration of local anesthesia
*.*

Objectives are:
1.To evaluate the effect of kaleidoscope to reduce dental anxiety levels in young children before and after the administration of local anesthesia.2.To evaluate the effect of virtual reality goggles to reduce dental anxiety levels in young children before and after the administration of local anesthesia.3.To compare effect of kaleidoscope and virtual reality goggles technique to reduce dental anxiety levels in young children before and after the administration of local anesthesia.

This parallel randomized multiple-arm clinical trial will be conducted in an isolated setup over a period of six months. It will be a trial for equivalence. Children from five - eight years old who are healthy, co-operative but anxious. Children without any past dental experience those will undergo dental treatment requiring administration of local anesthesia for procedures like pulpectomy or extractions will be included in the study. Children with known vision problems, psychological abnormalities, children with special health care needs, children suffering from systemic diseases, and the parents that are unwilling to participate will be excluded from the study.

**Group 1 – Kaleidoscope:** The children will be given a kaleidoscope having various changing colours and patterns to watch through just before the starting of the procedure and will be asked to watch through it until the procedure ends.

**Group 2 – Virtual reality goggles technique:** The children will be asked to wear Virtual Reality goggles and a video to keep the child engaged will be played by clicking on the remote control. VR will be given just before the starting of the procedure and will be asked to watch through it until the procedure ends.

**Group 3 –** Control group wherein usage of basic behavior guidance techniques like tell-show-do, ask-tell-ask, positive reinforcement, modelling, systemic desensitization and voice control will be employed.

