It is a randomized clinical trial. This is a version 1 of the protocol. Sequence generation by lottery method will be generated. The co-investigator of the department will generate the allocation sequence and will assign participants to interventions. It will be a double-blind study where trial participants, data analysts will be blinded. Data management by double data entry will be done. Personal information about potential and enrolled participants will be collected and maintained in order to protect confidentiality before, during, and after the trial. Comparators Kaleidoscope, Virtual reality goggles technique and conventional behaviour management method will be taken into consideration for comparing as all of them are interventions aiding for reducing the anxiety levels.

The sample size calculation is based on previous research by Aditya
*et al.*
^
13
^ that used a similar study technique by using the sample size formula for difference between two means,

$\frac{{\left(z\alpha +z\beta \right)}^{2}\left({\delta_{1}}^{2}+\delta_{2/k}^{2}\right)}{{∆}^{2}}$.

A total of 60 children will be included for the study. The participants in each group will be allocated by simple random sampling.

VFAS score using a validated Visual Facial Anxiety Scale is the primary outcomes to be measured. Pulse oximeter to measure physiological signs of oxygen saturation, and pulse rate, respiratory rate are the secondary outcomes to be measured. All the outcomes will be measured before, during, and immediately after the LA intervention.

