### Ethical considerations

Ethical approval for the study was obtained from the Institutional ethics committee of Datta Meghe Institute of Medical Sciences (Deemed to be University) [ref no: DMIMSU (DU)/IEC/2022/756].

The study protocol will be explained to the participating children and their parents.

Further, a written informed consent will be obtained from their parents.

Trial Registration is done under The
*Clinical Trials Registry - India*, the registry number is (CTRI/2023/04/051258- REF/2023/03/065058)

Date of Registration: 03/04/2023

https://ctri.nic.in/Clinicaltrials/rmaindet.php?trialid=83188&EncHid=56660.93573&modid=1&compid=19

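### The protocol calls the trial double-blind with blinded participants, but children can see which of the three arms they are in; only the data analysts can be blinded

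*Protocol article*

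**What the plan says.** The blinding statement in the Protocol section reads: "It will be a double-blind study where trial participants, data analysts will be blinded". It names two blinded parties, participants and data analysts. Operators and outcome assessors are not mentioned.

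The arms are described in the same section:

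- Group 1: "The children will be given a kaleidoscope having various changing colours and patterns to watch through just before the starting of the procedure", with viewing to continue until the procedure ends.
- Group 2: "The children will be asked to wear Virtual Reality goggles and a video to keep the child engaged will be played", again until the procedure ends.
- Group 3: "Control group wherein usage of basic behavior guidance techniques like tell-show-do, ask-tell-ask, positive reinforcement, modelling", followed by further guidance techniques. No device or sham device is mentioned.

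Under Ethical considerations: "The study protocol will be explained to the participating children and their parents".

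On the primary outcome: "VFAS score using a validated Visual Facial Anxiety Scale is the primary outcomes to be measured". On timing: "All the outcomes will be measured before, during, and immediately after the LA intervention". The rater is not stated.

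**The concern.** Blinding participants means that they do not know which intervention they receive. Here each intervention is something the child looks through, wears, or goes without, so the child sees the allocation as soon as treatment starts. The article claims a property that its own arm descriptions rule out.

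This matters because the primary outcome is an anxiety score. Such a score can be moved by novelty, by expectation or by a wish to please if the child gives it, and by the rater's own expectation if an observer gives it. A reader told that the trial is double-blind would discount both routes, and the label would carry into the trial report and any later risk-of-bias judgement.

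**Working it through.** The main check is one of consistency. The article states no figure for blinding, so there is none to reproduce.

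**Each party set against the arm descriptions**

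| Party | Named as blinded? | Can be blinded as described? |
|---|---|---|
| Child | Yes | No. Kaleidoscope, goggles and no device are plainly different, and no sham or masking is described. |
| Data analyst | Yes | Yes, with coded arms. |
| Operator | No | No. The article makes no claim here. |
| VFAS rater | No; rater not stated | If the child, no. If an observer, not for the rating during the procedure, when the device is in use. |

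One of the two parties on which the label rests drops out. Explaining the protocol to child and parent makes it harder still to suppose that the child does not recognise the arm.

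**Does the point depend on who rates the VFAS?** No.

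- If the child rates, the rating is made by someone who knows the arm.
- If an observer rates, the devices stay in use until the procedure ends and one rating is taken during it, so that rating is made with the device in view. Assessors are not among the blinded parties.

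**Illustration of what an unblinded rating could do**

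Inputs:

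- 60 children in total (Protocol section).
- n = 20 per arm, which is 60/3. This is an assumption: equal arms are not stated, and simple random sampling does not guarantee them.
- Significance level 0.05 (Data analysis and statistical plan). Two-sided testing is an assumption.
- No true effect, and a reporting shift of b SD between two arms. The values of b are assumptions and do not come from the document.

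The two-sample t statistic then has 2 × 20 − 2 = 38 degrees of freedom, critical value 2.024 and noncentrality λ = b × √(n/2) = b × √10. The false-positive rate is P(|T| > 2.024) under the noncentral t distribution.

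| b (SD) | λ | False-positive rate |
|---|---|---|
| 0 | 0 | 5.0% |
| 0.2 | 0.632 | 9.5% |
| 0.3 | 0.949 | 15.2% |
| 0.4 | 1.265 | 23.4% |
| 0.5 | 1.581 | 33.8% |

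The table shows how sensitive a comparison of this size is to a modest shift. It does not estimate this trial's error rate.

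**The case against.** The strongest reply is that the fault lies in a label. The arms are openly described, so an attentive reader would see that children know what they receive. No design could blind a child to these devices, and correcting the sentence leaves arms, sample size, endpoint and tests unchanged. The article also already blinds the analysts, takes a measurement before the local anaesthetic, and has pulse oximetry as a secondary outcome. All of that is true. It does not make the sentence correct, and the sentence is what others will rely on when they judge bias in the primary outcome.

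One could also read the claim as blinding to the hypothesis only. The article describes no such arrangement. Explaining the protocol is not proof that the hypothesis is disclosed, and children without past dental experience may hold weaker expectations about which arm is better. That may reduce the bias, but it does not make participants blind to their arm.

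Four stronger readings are tempting and are not supported:

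- **That the VFAS is self-reported, with the treating team present.** The article says neither. It uses the term self-reported only in the Discussion, for a different scale in an earlier study.
- **That the control children are untreated.** They have no device but receive active behaviour guidance.
- **That the trial's false-positive rate is 9.5% to 34%.** Those figures rest on an assumed shift and on assumed equal arms. They also fit a device-versus-control contrast best, and none of the three listed objectives tests that contrast: two are before-and-after within a device, and the third is kaleidoscope versus goggles, where both arms get a device and a novelty effect would at least partly cancel. The trial is also described as one for equivalence, where a false positive means something else.
- **That the protocol wrongly claims a blinded operator.** It makes no such claim.

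**Conclusion.** The point holds. Participant blinding is incompatible with the three arms as described, analyst blinding is the only blinding achievable among the parties named, and double-blind overstates the protection of the VFAS outcome. This conclusion rests only on the article's own text and needs no numerical assumption.

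The size of the resulting bias is unknown. It is of most concern for a device against active guidance and of less concern for kaleidoscope against goggles. Whether it would be the child's response bias or an assessor's bias depends on who scores the VFAS, which the article leaves open. Delivering these interventions unblinded is unavoidable and acceptable; the defect is the claim that participants are blinded. The study status is given as yet to be started, so the correction can be made before enrolment.

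**What to change.** 1. Replace the blinding sentence with: open-label for participants and operators; data analysts blinded to arm codes until the primary analysis is locked.
2. Record the baseline VFAS before the arm is revealed to child, parent and rater.
3. Use one identical VFAS script in all three arms.
4. State who scores the VFAS, and that this person is not masked while the devices are in view.
5. State response or assessor bias as a limit on the VFAS conclusion, mainly for device versus active guidance and less so for kaleidoscope versus goggles.

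The cost is protocol wording and a small change in the order of steps at the chairside, with no extra staff and no change in sample size. If the registry entry, which was not available here, repeats the claim, it needs the same correction. The downside is a less favourable design label.

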### Data analysis and statistical plan

Analytical tests like Chi square test and student’s t-test will be performed. All the statistical analysis will be performed using SPSS software, version 27.0 p<0.05 will be considered as the level of significance. This randomized clinical trial will be conducted at the Department of Pediatric and Preventive Dentistry, Sharad Pawar Dental College, Datta Meghe Institute of Higher Education and Research, Wardha. The allocation will be done using lottery method.

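### Two-group tests at an unadjusted 0.05, in a three-arm trial with no designated primary VFAS time point or contrast, leave the false-positive rate on the primary outcome at about 7% to 23%, depending on the reading

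*Protocol article*

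**What the plan says.** All references are to the protocol article.

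- **Tests and threshold** (Data analysis and statistical plan): "Analytical tests like Chi square test and student’s t-test will be performed", and "p<0.05 will be considered as the level of significance". The section gives no order of testing, no adjustment and no test for three groups.
- **Arms** (Protocol): kaleidoscope, VR goggles and a control group managed with basic behaviour guidance. All three enter the comparison: "Comparators Kaleidoscope, Virtual reality goggles technique and conventional behaviour management method will be taken into consideration for comparing".
- **Primary outcome** (Protocol): "VFAS score using a validated Visual Facial Anxiety Scale is the primary outcomes to be measured". No time point is attached to it.
- **Secondary outcomes** (Protocol): "Pulse oximeter to measure physiological signs of oxygen saturation, and pulse rate, respiratory rate are the secondary outcomes to be measured".
- **Timing** (Protocol): "All the outcomes will be measured before, during, and immediately after the LA intervention".
- **Objectives** (Protocol): the first two concern change within each device arm. The third is between arms: "To compare effect of kaleidoscope and virtual reality goggles technique to reduce dental anxiety levels in young children before and after" the anesthetic is given. The three are not ranked, and none mentions the control arm.
- **Framework** (Protocol): "It will be a trial for equivalence". No margin is given.

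**The concern.** A t-test compares two means. Three arms give three pairs, and VFAS has two readings after the distraction has begun, so up to six between-arm comparisons can each claim to be the primary result. Each would be judged at 0.05. The 5% level then describes a single test and not the trial's main conclusion.

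At stake is selective reporting that nobody could detect. If one pair differs at one reading and the others do not, nothing in the article shows whether that pair and reading were the ones intended. The article says that the study has not started, so the choice can still be made without sight of data.

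**Working it through.** **The plan's own figures.** The article states no family-wise error rate, so there is none to reproduce. Its one design figure, 60 children, cannot be reproduced either, because power, standard deviations, difference and allocation ratio are not given.

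**Inputs from the article.** Three arms; 60 children; VFAS primary; three readings, of which two (during, immediately after) follow baseline; level 0.05 per test.

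**Assumptions.** Equal arms of 60 / 3 = 20; two-sided tests; no true differences between arms; normal data; correlation r between a child's two post-baseline readings varied from 0 to 0.9.

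**Step 1: count the comparisons on VFAS.**
- Pairs of arms: 3 × 2 / 2 = 3
- Post-baseline readings: 2
- All pairs at both readings: 3 × 2 = 6

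**Step 2: reference values if the tests were independent.** The chance of at least one false positive is 1 − 0.95^m.
- m = 2: 1 − 0.95² = 9.8%
- m = 3: 1 − 0.95³ = 14.3%
- m = 6: 1 − 0.95⁶ = 26.5%

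The tests are not independent: pairs share arms and readings share children. The true rates are therefore lower.

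**Step 3: simulate with that dependence.** 40,000 trials per setting, 20 per arm, pooled t-tests at two-sided 0.05. Entries are the chance of at least one p < 0.05.

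| r between readings | 3 pairs, one reading | Kaleidoscope vs VR, both readings | 3 pairs, both readings |
|---|---|---|---|
| 0 | 12.5% | 9.7% | 23.2% |
| 0.3 | 12.3% | 9.5% | 22.4% |
| 0.5 | 12.0% | 9.5% | 21.3% |
| 0.7 | 12.2% | 8.5% | 19.7% |
| 0.8 | 11.9% | 8.0% | 18.3% |
| 0.9 | 12.2% | 7.0% | 16.8% |

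The first column does not depend on r; its small differences are simulation noise. A repeat run with another seed agreed within half a percentage point in every cell.

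**Step 4: other readings of the text.**
- Six comparisons of change from baseline: about 21.5% at every r.
- The three objectives taken literally (a paired test in each device arm, plus kaleidoscope versus VR on change): 11% to 12%.

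**Step 5: what restores 5%.**
- One contrast named in advance at one time point: 5% by construction.
- A three-group F-test as gate at one chosen reading: about 5%.
- The same gate at both readings, with neither named primary: 7% to 10%. A three-group test alone is therefore not enough; the time point must also be fixed.

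**The case against.** The strongest reply is that this is one paragraph of a journal article. The word 'like' leaves the list of tests open, no test is assigned to any contrast or time, and a full protocol or analysis plan may hold the model and the order of testing. That stands as a reason not to fault the article for missing model detail, and it means the rates above apply to readings of the text and not to a stated procedure. It does not remove the point. The section does fix a threshold, and the tests it names are two-group tests that do not match the three-arm, repeated-reading design set out elsewhere in the same article.

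A second reply is that the third objective names kaleidoscope versus VR, the only between-arm contrast in the objectives and the one in the aim. This is correct, and it rules out saying that no contrast is named. But the objective is one of three unranked ones, the control arm is also to be compared, and even this single contrast at both readings gives 7% to 10%.

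A reader might infer more than the documents support:

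- **That the error rate is simply one in five.** That is the widest of several plausible readings on VFAS; narrower ones give 7% to 12%.
- **That all four outcomes form one error family.** The article separates VFAS as primary from the physiological measures as secondary, so a significant secondary result could not stand as the primary one.
- **That before-after data will be analysed with the unpaired test.** The article does not say so, and Student's t-test has a paired form.
- **That chi-square will be applied to VFAS.** The article does not assign it to any variable; it may be meant for categorical ones.

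**Conclusion.** The concern holds in limited form. The tests and threshold stated in the article do not keep the false-positive rate on the primary outcome at 5%, because neither a VFAS time point nor a contrast is designated as primary. The size depends on the reading: about 7% to 10%, 12%, or 17% to 23%, as set out above. No reading that uses more than one comparison reached 5%.

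These figures rest on equal arms of 20, two-sided tests, normal data, no true differences and an assumed range of correlation; the article supplies none of these. They concern false claims of a difference. The trial also calls itself an equivalence trial, and a plain t-test does not control a false claim of equivalence. That is a separate matter, but it bears on how the primary contrast is chosen.

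**What to change.** Before enrolment, amend the analysis section as follows.

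1. Name one primary VFAS time point. Immediately after local anesthesia is one option and matches the timing in the objectives.
2. Analyse it in one model with all three arms, adjusted for baseline VFAS, which is already collected.
3. Designate the primary contrast or contrasts so that they agree with the third objective and with the stated equivalence framework. Making only device-versus-control contrasts primary would demote the comparison that the aim names, so the sponsor has to settle this explicitly.
4. If more than one contrast is primary, use Holm's procedure or a fixed order at two-sided 5%.
5. Label the other time points, contrasts and physiological outcomes secondary, reported as estimates with 95% confidence intervals.
6. For clarity, state that before-after comparisons use the paired form and that chi-square is for categorical variables.

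**Cost.** With one primary contrast, the change is wording only. With two under Holm, the smaller p-value is tested at 0.05 / 2 = 0.025, at some loss of power. As an illustration only, since the article gives no effect size: 20 per arm has 80% power at 0.05 for a standardised difference of (1.960 + 0.842) × √(2/20) = 0.886. At 0.025 the normal approximation gives Φ(0.886 × √10 − 2.241) = Φ(0.56), about 71%. Restoring 80% needs 2 × (2.241 + 0.842)² / 0.886² = 24.2, so 25 per arm. A fixed order avoids this loss for the first contrast. Adjusting for baseline VFAS may recover part of it. Splitting 0.05 equally over all six VFAS comparisons would cost far more: power falls to about 56%, and about 31 per arm would be needed. Naming one time point is therefore the cheaper route.

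### The named between-arm tests are unadjusted although a pre-anaesthetic reading of every outcome is planned; ANCOVA on that reading would be more precise whether the t-test uses post values or change scores

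*Protocol article*

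**What the plan says.** The Protocol section of the article defines the primary outcome: "VFAS score using a validated Visual Facial Anxiety Scale is the primary outcomes to be measured". The secondary outcomes are physiological: "Pulse oximeter to measure physiological signs of oxygen saturation, and pulse rate, respiratory rate are the secondary outcomes to be measured". It then sets the schedule: "All the outcomes will be measured before, during, and immediately after the LA intervention". A pre-anaesthetic value of every outcome is therefore planned.

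Under Data analysis and statistical plan the article states: "Analytical tests like Chi square test and student’s t-test will be performed", and "p<0.05 will be considered as the level of significance". It does not say whether the t-test is paired or independent, whether it uses the post value or the change, or which time point it uses.

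On size and allocation: "A total of 60 children will be included for the study" and "The participants in each group will be allocated by simple random sampling". There are three arms and no stated ratio.

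All three objectives, including the comparison of the two devices, are worded in terms of anxiety before and after the anaesthetic. The same section calls the trial one for equivalence. On the timing of the device: "The children will be given a kaleidoscope having various changing colours and patterns to watch through just before the starting of the procedure"; virtual reality is timed in the same way.

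**The concern.** The trial is small and has three arms. A child's starting anxiety or pulse rate is likely to predict the later value, and the trial collects that starting value. Neither of the named tests conditions a between-arm comparison on it.

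Two things are at stake. The first is precision: variation between children that the baseline could explain stays in the error term. The second is chance imbalance: with about 20 per arm, arms can differ noticeably in starting anxiety. A post-value comparison carries part of that difference into the result, and a change-score comparison over-corrects for it.

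A related practical point is that the device is given shortly before the procedure and the first reading is taken before the anaesthetic, but the article does not say which comes first. That decides whether the reading can serve as a baseline.

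**Working it through.** **The plan's own figure.** The total of 60 cannot be reproduced. The article shows a formula for two means but gives no difference, standard deviations, power or allocation ratio. The figures below therefore illustrate the comparison of methods and do not check the sample size.

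**Inputs.**
- From the article: 60 children, three arms, significance level 0.05, readings before, during and after the anaesthetic.
- Assumed: equal arms, 60/3 = 20 each; a two-sided superiority test; a true difference of 0.8 SD; a baseline-outcome correlation r of 0.3, 0.5 or 0.7; equal variances at both times.

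**Step 1: the possible t-tests.**
- Independent t-test on post values: baseline is not used. Relative variance 1.
- Independent t-test on change scores: baseline is used with its slope forced to 1. Relative variance 2(1 − r).
- Paired t-test within an arm: this addresses the two single-device objectives as worded, but gives no between-arm contrast, so it cannot serve the third objective.
- For reference, ANCOVA has relative variance 1 − r². Its ratio to the change score is (1 − r²)/[2(1 − r)] = (1 + r)/2, which is below 1 for every r < 1.

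**Step 2: power.** The effective standardised difference is 0.8 divided by the square root of the relative variance. Power is from the noncentral t distribution with 20 per arm and 38 degrees of freedom. Giving up one degree of freedom for the covariate lowers the ANCOVA figures by less than 0.1 point.

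| r | Post value: variance, power | Change score: variance, power | ANCOVA: variance, power |
|---|---|---|---|
| 0.3 | 1.00, 69.3% | 1.40, 54.9% | 0.91, 73.4% |
| 0.5 | 1.00, 69.3% | 1.00, 69.3% | 0.75, 81.2% |
| 0.7 | 1.00, 69.3% | 0.60, 88.9% | 0.51, 93.2% |

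The gain from ANCOVA over post values is about 4, 12 and 24 points. Over change scores it is about 18, 12 and 4 points.

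**Step 3: equivalence.** The width of a confidence interval scales with the square root of the variance. Relative to post values, ANCOVA multiplies the width by √0.91 = 0.95, √0.75 = 0.87 and √0.51 = 0.71. Relative to change scores the factors are √0.65 = 0.81, √0.75 = 0.87 and √0.85 = 0.92. This holds whichever hypothesis the interval serves.

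**Step 4: chance imbalance.** The standard error of the baseline difference between two arms is √(2/20) = 0.316 SD. The probability that a given pair differs by more than 0.5 SD is 2[1 − Φ(0.5/0.316)] = 11.4%. The probability that at least one of the three pairs does so is about 25% (simulation). Given a 0.5 SD imbalance, the expected shift in the contrast is:
- post value, r × 0.5: 0.15, 0.25 and 0.35 SD at r = 0.3, 0.5 and 0.7;
- change score, (r − 1) × 0.5: −0.35, −0.25 and −0.15 SD;
- ANCOVA: zero in expectation.

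**The case against.** The strongest reply is that the article never says that baseline will be ignored. Its list of tests is open-ended, the t-test is not defined, and the objectives speak of before and after. A reader might infer from the bare mention of a t-test that the baseline values are discarded; the text does not support that, since a change-score or paired test is at least as natural a reading. This stands, and the point does not depend on it: both between-arm readings are less precise than ANCOVA.

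It can also be said that an unadjusted t-test is valid, and that covariate adjustment is often left to an analysis plan not shown here. Both are true. The point rests on the method that the article does name, and on a better one being available from data already planned.

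A reader might also infer that chance imbalance biases the trial. It does not: averaged over randomisations the contrast is unbiased, and the t-test's standard error allows for such imbalance. The shifts above are errors conditional on an imbalance that has occurred.

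The size of the gain can fairly be questioned. The correlation, the 0.8 SD difference and 20 per arm are not in the article, and simple randomisation does not guarantee equal arms. The power figures are for superiority, whereas the article says equivalence. Against change scores the gain is modest when r is high.

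Finally, a reader might infer that the first reading is taken with the device already in use. The article does not give the order, so this is only a possibility. It matters because adjusting for such a reading could remove part of the effect.

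**Conclusion.** The point holds as a precision improvement worth making, not as an error that invalidates the trial. The named tests do not condition the between-arm comparison on a baseline that the trial plans to collect, and ANCOVA does better under either between-arm use of the t-test. Its variance is lower by 9% to 49% against post values and by 35% to 15% against change scores, for r from 0.3 to 0.7.

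That ANCOVA has the smaller variance follows from the formulas for any r strictly between 0 and 1. The size of the gain depends on the assumed correlation, and the power figures also on the assumed arm size, difference and superiority test. The advantage also requires a baseline reading that the device has not affected, which the article does not yet secure.

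**What to change.** For the between-arm comparisons, replace the t-test with ANCOVA: the post-anaesthetic value of the anxiety score as outcome, with arm and the child's own baseline value as covariates. Do the same for pulse rate, oxygen saturation and respiratory rate. Report adjusted differences with 95% confidence intervals; these also serve the stated equivalence aim.

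State that the baseline reading is taken before any device is handed over, so that adjustment does not remove part of the effect.

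This needs no additional children and no new measurement. The small downside is a fixed order for a reading already planned. The article gives the study as not yet started, so the change can be made before any data exist.
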